#### Analysis

##### Data confidentiality

This is an investigator initiated unblinded study. Personal medical data will be available to the investigators. During data analysis and for presentation and publication purposes data will be anonymized.

##### Data handling

Data will be entered by AB. Quality control will be performed routinely by three students (AB, OK, and AR) using double data entry and range checks for data values. Analysis will be performed by SPSS software (IBM SPSS Statistics for Windows, Version 24.0; IBM Corp.). *P* values will be compared to the value of *p* = 0.05 or less (taking into account multiple comparisons using the Benjamini-Hochberg [54]).

##### Pre-analysis

Before analysis is performed, the following will be carried out/recorded for each continuous variable:
Minimum and maximum values (as part of quality control)Mean ± standard deviation (SD)Normality test (distribution and Kolmogorov-Smirnov)Number of subjects included with no missing dataFor categorical variables a proportion will be calculated and presented with the number of patients.

##### Baseline comparisons

To test differences in continuous variables between the study groups the one-way analysis of variance (ANOVA) test will be performed (or Kruskal–Wallis one-way analysis of variance when normal distribution is rejected). For comparison of dichotomous or categorical variables the Chi square test will be performed.

The primary endpoints (% change in LBM and change in weight) will be analyzed using the analysis of covariance (ANCOVA) after 10 weeks and after 20 weeks (for diet and drug arms only) including several factors and covariates. Table 2 indicates the list of covariates and factors. Table 3 indicates the different outcomes and appropriate statistical method.

**Table 2 Tab2:** List of potential covariates and factors (partial list)

Factor or covariate	Type	Defined as
Treatment	Factor	SGLT2 inhibitor, diet, CRT
GLP1 agonists	Factor	Yes, no
Baseline body weight/ BMI	Covariate	–
HbA1c (%)	Covariate	–
Caloric consumption (Kcal)	Covariate	–
Resting metabolic rate (Kcal)	Covariate	–
Body fat %	Covariate	–
Strength (kg)	Covariate	–
Frailty or sarcopenia status	Factor	Frail or sarcopenic, pre-frail or pre sarcopenic and robust

*Abbreviations*: *BMI* Body Mass Index, *CRT* Circuit Resistance Training, *GLP-1* Glucagon-Like Peptide-1, *HbA1c* Hemoglobin A1C

**Table 3 Tab3:** The different outcomes and appropriate statistical method (partial list)

	Endpoint type	Statistical method
Primary outcome		
Change in body weight (%) from baseline to 10 weeks or to 20 weeks	Continuous	ANCOVA
Change in % lean body mass from baseline to 10 weeks or to 20 weeks	Continuous	ANCOVA
Proportion of participants having lost ≥2.5% at week 10 and 20	Binary	Logistic regression
Secondary outcomes		
Change in waist circumference from baseline to 10 weeks or to 20 weeks	Continuous	ANCOVA
Change in FPG and HB1Ac from baseline to 10 weeks or to 20 weeks	Continuous	ANCOVA
Change in sarcopenia and frailty status (improved vs. not improved; change from one level to the other) at week 10 and 20	Binary	Logistic regression
Change in strength and other functional abilities from baseline to 10 weeks or to 20 weeks	Continuous	ANCOVA
Change in systolic blood pressure from baseline to 10 weeks or to 20 weeks	Continuous	ANCOVA
Change in quality of life (improved vs. not improved; change from one level to the other) at week 10 and 20	Binary	Logistic regression

*Abbreviations*: *ANCOVA* Analysis of Covariance, *FPG* Fasting Plasma Glucose, *HbA1c* Hemoglobin A1C

Primary analysis will be intent to treat analysis. It will include all patients that had been randomized, started protocol and reached the end of the trial examinations (or last observation available will be imputed as their “end of study value”). Per protocol analysis will be performed by the a-priori conditions: a) for participants who had high compliance to workout (≥ 2/3 of sessions); b) for participants who had high compliance to diet (≥ score 9 in the Med-diet score and/or caloric consumption change from baseline was not more than 15% of report at baseline); c) for participants who had high compliance to drug therapy (≥80% tablets taken); d) for participants who did not violate the protocol (for example: changed thier habitual diet in the CRT arm; initiated new physical activity other than the one prescrived by us, ect.).

Sensitivity analysis can include all the participants who finished the trial including dropouts, with imputation of the last observation. This will be compared to an analysis which includes only participants that fully completed the study (have an assessment at the end of study).

We may also perform a mixed model for repeated measurements based on assessments of participants who completed the study and had high compliance to the treatment. An unstructured covariance matrix for measurements within the same participant will be employed, assuming that measurements for different participants are independent. The covariates and factors in Table 2 will be nested in the model.

Last, subgroup analysis will be done by stratification to several factors shown in Table 2, where ANCOVA or logistic regression models will be performed according to the outcome assessed (Table 3).

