#### Assignment of intervention

##### Allocation

At the end of Visit 2- subjects will be randomized at a ratio of 1:1:1 to each study group and stratified based on gender. Randomization will be conducted by a randomization software (computer generated random numbers) [34]. A third party who is not aware of research protocol will allocate patients into the study groups a priori to first recruitment using the randomization software and will create and keep the allocation list. Once recruitment for a particular baseline day and all baseline measurements are finished, a mediator in the IEMH (secretary) will contact the third party to reveal the allocations of the participants recruited and examined so far (allocation concealment).

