### Statistical methods

#### Sample size

The sample size calculation is based on the assumption that the mean difference in weight after 10 weeks between the empagliflozin arm and the CRT arm will be − 3.2 Kg. We assumed that the weight will not change in the CRT only group (body composition may change) and, based on the literature, that empagliflozin treatment causes a reduction in weight of ≈ 3–3.5 Kg. For 80% power and significance level of 5% each arm should include 40 subjects (*n* = 120 total). Another calculation was based on ANOVA for the comparison of three groups. We assumed that body fat % at the end of study will be 37, 36 and 40% for the diet, drug and CRT arms, respectively, with a 6% SD in each group. These assumptions are based on unpublished data obtained in a pilot study conducted in the IEMH. Assuming an attrition of ~ 10% we intend to recruit 120 up to 140 participants. Power calculations were performed using the G*Power Statistical Power Analyses for Windows [53].

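### Baseline differences between randomised arms are significance-tested to no purpose, while the primary ANCOVA covariates stay open and gender, the stratification factor, is not among those listed

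*Protocol article*

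**What the plan says.** Four places in the protocol article bear on this.

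- **Baseline comparisons, first paragraph.** For continuous variables: "To test differences in continuous variables between the study groups the one-way analysis of variance (ANOVA) test will be performed", replaced by Kruskal-Wallis when normality is rejected. For the rest: "For comparison of dichotomous or categorical variables the Chi square test will be performed". No purpose is given for the tests, and the variables are not listed or counted.
- **Allocation.** "subjects will be randomized at a ratio of 1:1:1 to each study group and stratified based on gender". A third party holds the allocation list, and the assignment is revealed only later: "Once recruitment for a particular baseline day and all baseline measurements are finished".
- **Baseline comparisons, second paragraph, and Table 2.** The primary endpoints (percentage change in lean mass, and change in weight) are analysed by ANCOVA with an unspecified number of factors and covariates. Table 2 is headed "List of potential covariates and factors (partial list". Besides treatment it has eight rows: GLP1 agonists, baseline weight or BMI, HbA1c, caloric consumption, resting metabolic rate, body fat %, strength, and frailty or sarcopenia status. Gender is not among them, and neither is baseline % lean mass.
- **Data handling.** P-values are compared with 0.05, "taking into account multiple comparisons using the Benjamini-Hochberg". The family of tests is not defined.

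**The concern.** A significance test asks whether a difference could have arisen by chance. When the groups were formed by concealed randomisation after the measurements were taken, the answer is already known: among all randomised patients, every baseline difference arose by chance. A small p-value does not show that randomisation failed, and a large one does not show that an imbalance is harmless.

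The tests would be merely superfluous if the covariates were fixed elsewhere in the article. They are not. The same section plans the baseline tests and then an ANCOVA that draws on an open list. If a covariate entered because its baseline p-value was small, it would enter by chance rather than for its relation to the outcome, and the treatment p-value would depend on a choice made after the data were seen. Gender was important enough to stratify on, but it is not named for the model. Where a stratification factor is related to the outcome, omitting it gives up precision.

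**Working it through.** The article states no figure for the baseline tests, so there is nothing of its own to reproduce on this point.

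**Are these really baseline tests between randomised arms?** Yes. They stand under the heading Baseline comparisons and compare the study groups. Table 3 assigns every outcome it lists to ANCOVA or logistic regression, and none to ANOVA or chi-square. The comparison of included with excluded subjects, under Visit 1, is a different one and is not affected.

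**Inputs**
- Test level: 0.05 (Data handling).
- Arms: three, with 40 subjects each (Sample size: "For 80% power and significance level of 5% each arm should include 40 subjects").
- Number of baseline tests, k: *assumption*. The eight covariate candidates in Table 2 give a low value. The schedule in Table 1 and the measurement sections suggest several dozen variables, so 20 and 40 are also shown.
- Correlation between baseline variables: *assumption*, 0 to 0.5. Weight, BMI, fat and lean mass are plainly related.

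**Independent, unadjusted tests.** The expected number of false positives is 0.05k, and the chance of at least one is 1 − 0.95^k.
- k = 8: expected 0.4; 1 − 0.95^8 = 0.34
- k = 20: expected 1.0; 1 − 0.95^20 = 0.64
- k = 40: expected 2.0; 1 − 0.95^40 = 0.87

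**Correlated tests.** Normal variables with equal pairwise correlation were simulated in 3 arms of 40, with one-way ANOVA on each variable and 4,000 runs. The chance of at least one p < 0.05 was:

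| k | correlation 0 | correlation 0.3 | correlation 0.5 |
|---|---|---|---|
| 8 | 33% | 31% | 26% |
| 20 | 65% | 55% | 42% |
| 40 | 87% | 75% | 57% |

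The zero-correlation column agrees with the formula. Correlation leaves the expected number of false positives unchanged but gathers them into fewer trials.

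**If Benjamini-Hochberg were applied to the baseline tests as a family of their own**, the chance of any flagged imbalance in the same simulations was about 4% to 5% at every k.

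**Covariates.** Setting Allocation beside Table 2: the stratification factor is gender, and Table 2 does not list it. Body weight is offered as an alternative to BMI, so even the baseline value of the weight outcome is not fixed. For lean mass, the nearest listed variable is body fat %, which is roughly its complement.

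**The case against.** The strongest reply is that no decision hangs on these tests. No sentence lets a baseline p-value select a covariate, trigger an adjustment or change a conclusion. Table 2 reads like a list chosen on clinical grounds, and for the optional mixed model the article says that the Table 2 terms go into the model. Means, SDs and proportions are already planned under Pre-analysis. A condensed article may also leave the final covariate set to a fuller document. Most of this stands, and it is why the point is minor. It does not give the stated tests a purpose. It also does not close a list that the article itself calls partial and potential.

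Three stronger readings are tempting, and the documents do not support them.

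- *Baseline p-values will choose the covariates.* The text leaves this possible but does not plan it.
- *Baseline tests will crowd the Benjamini-Hochberg family and cost the efficacy tests power.* Nothing places them in that family. This reading also conflicts with the high imbalance rates, which assume tests left unadjusted.
- *A false imbalance is practically certain.* Even with independence the figure is 64% to 87% for 20 to 40 tests. It is lower with correlation, and about 4% to 5% if the baseline tests are adjusted as their own family.

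One limit also applies. The null is true by design for all randomised patients. The primary analysis set, described after Table 3, requires that patients started the protocol and have a final or last observation, so losses after randomisation could disturb the balance. A baseline p-value would not repair that.

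**Conclusion.** The point holds in limited form. The planned tests of baseline differences between concealed-randomised arms are uninformative. If 20 to 40 variables are tested without adjustment, at least one chance imbalance has a probability of 64% to 87% under independence, or about 42% to 75% at correlations of 0.3 to 0.5. The number of tests and the correlations are assumptions, and the rates apply only if no multiplicity adjustment covers these tests.

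The consequence for the primary analysis is a possibility that the text leaves open, not a stated plan. The ANCOVA covariates are not fixed, and gender is not among those listed, so a choice steered by chance imbalance is not ruled out. The precision to be gained from including gender cannot be computed from the article. Severity is minor: the stated sample size and the definitions of the endpoints are unaffected.

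**What to change.** Make two changes to the Baseline comparisons section.

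1. Replace the ANOVA, Kruskal-Wallis and chi-square tests with a descriptive table by arm: mean and SD, or median and interquartile range, for continuous variables, and counts and proportions for categorical ones, without p-values.
2. State that the covariates of the primary ANCOVA are fixed in advance and do not depend on observed imbalance. They should be at least the baseline value of the outcome (body weight for the weight endpoint, % lean mass for the lean-mass endpoint) and gender. Use the same set at 10 and at 20 weeks. Any further Table 2 term kept for the primary model should be named now, on prognostic grounds; the others belong in sensitivity analyses.

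The cost is a few sentences. Weight and body composition are already measured on the baseline day, and gender is known for the stratification. No data collection, staffing or sample size changes.

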Functional and frailty tests	X					X		X
CRT diary (report on training days and performance)			X	X	X	X	X	X
Left of tablets count of drugs						X		X
Adherence to MedD	X					X		X
Food diary – 3 days			X			X		X
Quality of life	X					X		X
Phone calls (adverse events monitoring)			X	X	X	X	X	X
Encouragement using phone calls			X	X	X	X	X	X

^a^Allocation concealment until the end of baseline day – then allocation is introduced both to researcher and the subjects. Subjects allocated to SGLT-2 would meet physician at the end of the day for instruction of the use of the drug and will be supplied with drugs for 20 weeks). Subjects allocated to Diet and CRT groups will make an appointment for the following week (familiarization)

^b^For diet subjects – on site visit and for CRT subjects – familiarization at their homes

^c^At this week CRT group will finish the study and SGLTT-2 and V-Med add CRT on top of their current intervention. Familiarization of the CRT will be performed on the same week.

*Abbreviations*: *BIA* Bioelectrical Impedance Analysis, *BMI* Body Mass Index, *CRT* Circuit Resistance Training, *HbA1c* Hemoglobin A1C, *MedD* Mediterranean Diet

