#### Nutritional intake

Based on the food records obtained by a registered nutritionist (AB) the total energy intake and the proportion of carbohydrates, proteins, and fats as well as several micronutrients will be calculated in the three interventional groups.

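### Table 2 offers caloric intake, with no time point, as a covariate for the primary ANCOVA, and every scheduled food diary comes after allocation is disclosed

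*Protocol article*

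**What the plan says.** Under Baseline comparisons, the two primary endpoints named there (% change in lean body mass and change in weight) are to be analysed by ANCOVA with several factors and covariates: "Table 2 indicates the list of covariates and factors". Table 2 is titled "List of potential covariates and factors (partial list"). It contains "Caloric consumption (Kcal"), with a dash where the definition would go. Only one row carries a baseline label: "Baseline body weight/ BMI". The same table also feeds the optional mixed model and the subgroup analyses.

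The Nutritional intake section gives the source of energy intake: "Based on the food records obtained by a registered nutritionist". In Table 1 the row "Food diary – 3 days" is marked at familiarization (W0-2), week 10 and week 20. It is not marked at screening or on the baseline day. Footnote a to Table 1 reads "Allocation concealment until the end of baseline day – then allocation is introduced both to researcher and the subjects".

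Two other statements bear on the point. Table 1 marks a food frequency questionnaire at screening. The per-protocol definition compares caloric consumption with a baseline report, without naming the instrument.

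The Allocation section says "subjects will be randomized at a ratio of 1:1:1 to each study group and stratified based on gender". Gender does not appear in Table 2.

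**The concern.** ANCOVA in a randomised trial estimates the total treatment effect when its covariates cannot have been influenced by the assignment. Here the only records from which the article says it calculates energy intake are all completed once the participant knows the arm, in an open-label trial. The Blinding section also leaves the nutritionist who collects food intake unblinded.

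Intake is not a nuisance variable in this trial. The abstract names caloric restriction as the diet's route to negative energy balance, and the adherence section uses the week 10 and week 20 food records to judge adherence to the diet. The Background expects compensatory hyperphagia with SGLT-2 inhibitors and exercise, so later intake may move in the other arms as well. Conditioning on a variable that treatment changes would leave a primary analysis, described as intent to treat, that no longer answers the total-effect question for the diet arm.

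**Working it through.** The plan has no figure of its own on this point to reproduce, and the sample size is not in dispute. The check is one of timing, followed by an illustration of size.

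**1. Timing**

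| Item | Where stated | When | Relative to disclosure |
|---|---|---|---|
| Food frequency questionnaire | Table 1 | Screening (Visit 1) | Before |
| Allocation disclosed; drug arm instructed and supplied | Table 1, footnote a | End of baseline day (Visit 2) | – |
| First 3-day food diary | Table 1 | Familiarization (W0-2) | After |
| Later food diaries | Table 1 | W10, W20 | After, on treatment |

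Footnote a has the diet and CRT arms make their familiarization appointment for the week after the baseline day. Visit 3 is on site only for the diet arm, to meet the dietitian. The first diary is therefore completed after disclosure and in circumstances that differ by arm.

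**2. Size if on-treatment intake is used (assumptions, not from the documents)**

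If a share *s* of the total diet effect passes through intake, the adjusted estimate is (1 − *s*) × total effect. For *s* = 0.25, 0.50 and 0.75 it keeps 75%, 50% and 25%.

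To express this as power a scale is needed, and the documents give no diet effect on weight. I borrow −3.2 kg, which the Sample size section assumes for empagliflozin versus CRT, purely as a scale. No SD is stated. The SD that makes 40 per arm give 80% power at two-sided 5% is 3.2 / [(1.960 + 0.842) × √(2/40)] ≈ 5.1 kg. I further assume that the diet lowers intake by 400 kcal, with a within-arm SD of 350 kcal. Simulated two-arm comparison, 40 per arm:

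| Share through intake | Adjusted estimate (kg) | Power, adjusted |
|---|---|---|
| 0% | −3.2 | 66% |
| 25% | −2.4 | 46% |
| 50% | −1.6 | 23% |
| 75% | −0.8 | 9% |
| 100% | 0.0 | 5% |

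Without the covariate, power is about 79%. Even with no mediation power drops, because intake is then correlated with arm.

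**3. Size if only the W0-2 diary is used (same scale)**

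Assume that habitual intake (SD 350 kcal) predicts weight change at 0.004 kg per kcal, that recording error has SD 150 kcal, and that knowing the arm shifts the diet arm's record. The fitted slope is 0.004 × 350² / (350² + 150²) = 0.00338 kg per kcal. The adjusted estimate is −3.2 + 0.00338 × |shift|:

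| Shift in diet arm's record | Formula (kg) | Simulated (kg) | Power |
|---|---|---|---|
| 0 kcal | −3.20 | −3.16 | 80% |
| −100 kcal | −2.86 | −2.81 | 71% |
| −200 kcal | −2.52 | −2.54 | 59% |
| −300 kcal | −2.19 | −2.20 | 46% |
| −500 kcal | −1.51 | −1.54 | 21% |

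With no shift there is no bias.

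**4. Gender**

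If gender explains 5% to 20% of outcome variance (assumed), including it multiplies the ANCOVA standard error by √0.95 = 0.975 to √0.80 = 0.894. Power that was 80% becomes 82% to 88%. Leaving gender out does not bias the estimate.

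**The case against.** The best reply is that this is an article, and that Table 2 is expressly a list of potential covariates and a partial one. The final covariates and their time points may be settled in a document that is not shown. Much of this stands, and it rules out several stronger readings.

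- A reader might infer that the primary ANCOVA will adjust for intake. The text lists it as a candidate only.
- A reader might infer that no dietary value at all precedes allocation. The screening questionnaire does, and the per-protocol definition presupposes some baseline caloric report. What can be said is that no diary-based value does.
- A reader might take the missing baseline label to mean an on-treatment value. HbA1c, resting metabolic rate, body fat and strength lack the label too, yet Table 1 measures them at or before the baseline day. Intake differs because its stated source has no mark there.
- A reader might treat the W0-2 diary as necessarily altered by treatment. The article does not say whether its three days fall before or after the first dietary guidance. If before, it may largely reflect habitual intake, though recorded by people who know their arm.
- A reader might infer that gender is excluded. A partial list cannot show that.

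The reply does not dispose of the point. The article names this covariate, states where energy intake comes from, and schedules that source after disclosure. Followed as written, even the earliest diary value is post-disclosure, and an open list leaves a choice among intake values with different meanings.

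**Conclusion.** The point holds as a defect of timing and definition that should be corrected. Caloric intake is offered for the primary model without a time point, and every diary that could supply it follows disclosure of allocation. Adjusting for week 10 or week 20 intake, or for a first diary altered by knowledge of the arm, would not estimate the total effect of the diet.

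For weight the distortion would tend towards no diet effect. No direction is derived for % lean mass, and the diet-versus-drug comparison could be disturbed through both arms. The size is not obtainable from the documents: the figures above rest on assumed mediation shares, shifts and SDs. It would be wrong to read them as a forecast in kilograms, because −3.2 kg is the plan's empagliflozin-versus-CRT assumption and not a diet effect.

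Gender is a separate and smaller matter of precision.

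**What to change.** - Hand out the first 3-day diary at Visit 1 and collect it at Visit 2, before allocation is disclosed. Alternatively, take baseline intake from the screening food frequency questionnaire and say so, or drop intake from the primary model.
- Restrict Table 2 to values obtained before allocation is disclosed, label each one as baseline, and name the instrument and visit for intake. State which instrument supplies the baseline report in the per-protocol definition.
- Report week 10 and week 20 intake as outcomes only.
- Add gender as a fixed factor in the primary models.

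The cost is one diary moved forward by about a week and an edit to Tables 1 and 2, with no extra visit. The downside is that a few diaries will come from people later excluded. Gender is already recorded and uses one degree of freedom per model.

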**Discussion:**

The combination and comparison of these diverse interventions to metabolic control may lead to better understanding of their mechanism of action with potential clinical implications in older individuals. Also, this study will provide evidence of the effectiveness of these interventions on delaying the progression from diabetes to sarcopenia and/or frailty.

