### Main ascertainment of response variables

#### Anthropometric and sarcopenia

Anthropometric measurements will be obtained following a uniform protocol. Height, weight, waist and hip circumference will be measured twice. LBM, skeletal muscle mass (SMM), fat mass (FM) and % fat will be evaluated by the direct segmental multi-frequency bioelectrical impendence analysis (BIA) technique method using the ‘In-Body 770 body composition analyzer’. The In-Body 770 is a valid tool for the assessments of total body and segmental body composition [40]. Sarcopenia will be assessed in line with the consensus definition offered elsewhere [41] using three parameters: a) low skeletal muscle mass; b) low muscle strength; c) low physical performance [41]. Pre-sarcopenia will be defined as low skeletal muscle mass but normal strength and physical performance, whereas sarcopenia will be defined as having both low muscle mass with either low muscle strength or low physical performance. Severe sarcopenia will be determined by the presence of all 3 criteria (low muscle mass + strength + low performance). Skeletal muscle mass will be obtained by the In-Body (770) body composition analyzer. Shortly, the skeletal muscle index (SMI = skeletal muscle mass/body mass × 100) will be compared to gender-specific reference norms of young adults (aged 18–39 years). Sarcopenia will be defined as any value < 10.76 kg/m^2^ for men and < 6.76 kg/m^2^ for women [42]. Low muscle strength and low physical performance will be assessed using grip strength and gait speed test as described in the following paragraph on frailty.

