#### Frailty

Will be assessed using a modification of the Fried assessment [43] based on low hand grip strength, low four meters average walking speed, low caloric expenditure on physical activity, self-reporting of extreme fatigue or low functionality and a spontaneous reduction of at least 4.5 kg in the past year. In this method, the low hand grip criterion is met when grip strength, assessed as the maximal result of 3 readings of the dominant hand by a handheld dynamometer [Jamar® Plus+ Digital Hand Dynamometer (Jamar® Smart) 200-lb.] is less than or equal to the gender- and body mass index–specific cutoff points provided by Fried et al. [43]. The slow gait speed criterion is met if the participant scored more than 4 s [44]. The 5-item FRAIL scale [45] which included the following 5 components: fatigue, resistance, ambulation, co-morbidity, and loss of weight. In both tools, frailty scores range from 0 to 5 (ie, 1 point for each component; 0 = best score, 5 = worst score) and are further categorized into: frail (3–5), pre-frail (1–2), and robust (0).

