#### Quality of life

Will be self-reported and assessed by the SF-12 (a shorter version of the SF-36). The SF-12 yields two summary scores: physical component summary and mental component summary. The SF-12 is strongly correlated with the SF-36 [51]. The SF-12 have been translated and validated in Hebrew in inclusive studies of population aged 18–75 years [52].

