## Discussion

Our study aims to evaluate the effectiveness of three different interventions (V-Med diet, CRT and empagliflozin, separately or in combination) on metabolic, anthropometric and physical function parameters in older subjects with T2DM. Several new facets of T2DM treatment in this age group are at the core of this study: 1. This is the first comparison of empagliflozin to lifestyle modification in older patients; 2. This is the first evaluation of a multistage lifestyle and empagliflozin therapy interventions on frailty and sarcopenia; 3. Our hybrid diet intervention (V-Med diet) has thus far not been tested in conjunction to CRT or compared to other treatment modalities; 4.This is the first study to assess the effect of a CRT program in older subjects with T2DM.

There are, however, several limitations to our study protocol: 1) the possibility for volunteer bias which might lead to the inclusion of highly engaged patients. This may affect only the external validity of the study, but not its internal validity; 2) the exclusion criteria include several co-morbidities that are likely prevalent in the older age and associated with diabetes such as recent stroke or myocardial infraction. While this may minimize the generalization of our results, subjects with these conditions may not benefit from our interventions; 3) the apparently narrow HbA1C range used as an inclusion criterion (6.5–8%), may also limit the generalization of our results at this age group. Still, we wish to minimize the effect of major reduction in glycemic values per se (associated with higher values of HbA1C at entry for the study) as a potential contributor to any observed improvements in functional and metabolic states; 4) given its relatively short duration and limited sample size the study is unlikely to evaluate morbidity outcomes such as the incidence of myocardial infraction or stroke.

The combination and comparison of the three interventions for metabolic control may lead to better understanding of their mechanism of action with potential clinical implications in older subjects with T2DM. This study may also provide evidence of the effectiveness of different interventions on the progression from diabetes to sarcopenia and/or frailty and their potential effect on the quality of life older subjects with T2DM.

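### Table 3 analyses SF-12, frailty and sarcopenia only as improved or not improved, so the status endpoint cannot show progression and the SF-12 scores lose over a third of their information

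*Protocol article*

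**What the plan says.** Two secondary-outcome rows of Table 3 (Baseline comparisons section) have endpoint type binary and method logistic regression. One is "Change in quality of life (improved vs. not improved; change from one level to the other) at week 10 and 20"; the other is "Change in sarcopenia and frailty status (improved vs. not improved; change from one level to the other) at week 10 and 20".

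The measures behind these rows are finer than that:

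- **SF-12** (Quality of life section): "The SF-12 yields two summary scores: physical component summary and mental component summary". No levels or cut-offs are given.
- **Frailty** (Frailty section): "In both tools, frailty scores range from 0 to 5", and the scores are then grouped as robust, pre-frail or frail.
- **Sarcopenia** (Anthropometric and sarcopenia section): ordered stages. "Pre-sarcopenia will be defined as low skeletal muscle mass but normal strength and physical performance", followed by sarcopenia and severe sarcopenia.

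On what the trial will show, the abstract's Discussion says "this study will provide evidence of the effectiveness of these interventions on delaying the progression from diabetes to sarcopenia and/or frailty". The main Discussion is more cautious: "This study may also provide evidence of the effectiveness of different interventions on the progression from diabetes to sarcopenia and/or frailty".

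**The concern.** Progression is a move to a worse level. In the listed endpoint that move is coded the same as no move at all: a participant who goes from robust to frail counts exactly like one who stays robust. Neither frailty nor sarcopenia is among the major inclusion criteria, so some participants will probably start at the best level. They cannot improve whatever their arm, but they remain in the denominator.

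For quality of life, a change from one level to another has no stated meaning, because the SF-12 scores have no levels in the article. Any split also discards information that ANCOVA would keep, and Table 3 uses ANCOVA for strength, function, blood pressure and the other continuous outcomes.

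At stake are the trial's ability to support its own statement on delaying progression and the precision of its quality-of-life comparison.

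**Working it through.** **Starting point.** The article gives no power figure for these three outcomes. Its general figure is 40 per arm for 80% power at 5%. The ANOVA inputs (means 37, 36 and 40, SD 6) give effect size f = 0.283 and power 0.789 at 40 per arm, which agrees with the stated 80% to within about a point. That figure does not bear on this point; only the 40 per arm is carried forward. All rates and effect sizes below are assumptions.

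**1. Splitting a normal score.** If a share p counts as improved, the relative efficiency of the split is φ(z_p)² / [p(1 − p)].

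| Share improved | Efficiency | Information lost |
|---|---|---|
| 50% | 0.637 (= 2/π) | 36% |
| 40% | 0.622 | 38% |
| 30% | 0.576 | 42% |
| 20% | 0.490 | 51% |
| 10% | 0.342 | 66% |

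The smallest possible loss is 36%. It exceeds half only when fewer than about 21%, or more than about 79%, improve.

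**2. What that does to power.** The standardised difference with 80% power at 40 per arm (two-sided 5% t test) is d = 0.634. Cut midway between the arms, the improved shares are Φ(−0.317) = 0.376 and Φ(0.317) = 0.624. Power at 40 per arm is then 0.608 by the normal approximation, with 63 per arm needed for 80%. Exact enumeration of the uncorrected chi-square test gives 0.635. Hence about 61–63%. With fewer improving, the same d gives 56% (20% vs 42% improved, 70 per arm needed) or 46% (10% vs 26%, 91 per arm needed).

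**3. Arms that differ only in worsening.** Assume 10% improve in both arms, 30% worsen in one and 5% in the other, with 40 per arm:

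- improved or not improved: rejection in about 5% of 4,000 simulated trials, which is the significance level;
- rank test on worse / same / better: 63%;
- worsened or not worsened: 85% (normal approximation) to 89% (exact enumeration).

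The first result does not depend on the rates chosen. If the improvement rates are equal, the listed endpoint is under its null hypothesis however much the worsening rates differ.

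**4. Ceiling.** Assume 20% vs 50% improve among those able to, and let r be the share at the best level at baseline. The observed rates become 0.20(1 − r) and 0.50(1 − r):

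| r | Rates | Power, all 40 per arm |
|---|---|---|
| 30% | 14% vs 35% | 59% |
| 50% | 10% vs 25% | 42% |
| 70% | 6% vs 15% | 26% |

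**5. The opposite case.** If the arms differ only in improvement (10% vs 30%, with 10% worsening in both), the binary endpoint has about 63% power and the rank test about 41%.

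**The case against.** These are secondary outcomes in a trial that calls itself exploratory, and Table 3 is headed a partial list. Strength and functional abilities are analysed as continuous changes by ANCOVA, and % lean body mass is a continuous primary outcome. Grip strength and gait speed feed both status definitions, so decline in the components would be visible. Table 2 lists baseline frailty or sarcopenia status as a factor and subgroup analyses by Table 2 factors are planned, so participants who cannot improve can be adjusted for or separated. An analysis plan, not shown, could define SF-12 levels. Only the abstract says will; the main Discussion says may.

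Most of this is fair and limits the point. A reader might infer that most of the information is discarded. The documents do not support that: a near-median split loses about 36–38%, no improvement rate is given, and the calculation assumes a normal score, so it is at most a guide for the short frailty and sarcopenia scales. A reader might also infer that the trial is blind to decline altogether; the continuous outcomes show otherwise. Nor is an ordinal model better in every case, as step 5 shows.

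Two things remain. None of these provisions makes worsening of status an endpoint: adjusting for baseline level or separating by it leaves worse and stable in one category. And the binary form of the quality-of-life row is a stated choice, which defining levels later would complete but not undo.

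**Conclusion.** The point holds in this limited form. As written, the status endpoint cannot detect a difference between arms in progression of frailty or sarcopenia; when arms differ only in worsening it rejects at about 5%. The abstract's claim on delaying progression therefore has no listed status endpoint behind it. This follows from the coding and needs no assumed rate.

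The SF-12 loss is at least about 36% for a normal score. The fall from 80% to about 61–63% power is illustrative: d = 0.634 was chosen because it gives 80% at 40 per arm and is not an SF-12 assumption of the trial. The ceiling figures rest on assumed shares at the best level and assumed improvement rates.

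This should be changed, but it concerns secondary outcomes and does not touch the analysis of body weight and lean mass.

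**What to change.** Revise the two rows of Table 3:

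1. **Quality of life:** analyse the SF-12 physical and mental summary scores as two continuous outcomes by ANCOVA adjusted for baseline, as for the other continuous outcomes in the table.
2. **Frailty and sarcopenia:** analyse the ordered levels (or the 0–5 frailty score) at weeks 10 and 20, adjusted for baseline level and gender, for example with a proportional-odds model.
3. **Progression:** list worsening of status as a separate endpoint beside the improvement rate. It addresses the claim directly and had the most power in step 3.

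If worsening is not added, soften the abstract's sentence on delaying progression.

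The cost is small. No new data are needed, since Table 1 already schedules these measures at screening, week 10 and week 20. Ordinal odds ratios are slightly harder to explain than a responder rate, rely on proportional odds, and can have less power than the binary endpoint if the arms differ only in improvement; keeping the improvement rate covers that case. The extra comparisons enter the planned Benjamini-Hochberg adjustment.
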